#### 2.3.3 Safety outcomes

The following items will be compared between baseline (month 0) and each of the observation and follow-up time points for imeglimin:1. Incidence of adverse events and diseases2. Liver function markers: measured values of aspartate aminotransferase (AST), alanine aminotransferase (ALT), and gamma glutamyl transpeptidase (γGTP)3. Lipid markers: measured values of total cholesterol, high-density lipoprotein (HDL)-cholesterol, and triglycerides (TG)4. Blood pressure, pulse rate, and body weight (measured values of systolic/diastolic blood pressure, pulse rate, and body weight) and calculated value of body mass index (BMI)

#### 2.3.4 Exploratory outcomes

1. Comparison of arteriosclerosis and inflammatory stress markers at baseline (month 0) and 6 months after administration and 3 months after withdrawal of imeglimin:

Arteriosclerosis markers: changes in brachio-ankle pulse wave velocity (baPWV) and toe-brachial pressure ratio (TBI) using a volume-plethysmographic apparatus (BP-203RPEIII; Omron Healthcare, Kyoto, Japan). The baPWV and TBI are measured by trained clinical technicians in a quiet and temperature-controlled clinical measurement room after the patient rested for >5 min in the supine position (Yamashina et al., 2002).

Inflammatory oxidative stress markers: changes in serum high-sensitivity C-reactive protein (hs-CRP) and urinary 8-hydroxydeoxyguanosine (8-OHdG).2. Stratified analysis and comparison by each antidiabetic drug

### 2.4 Handling of adverse events (AEs)

The INFINITY study will monitor safety by collecting AEs during the study period. An AE is defined as any medically unfavorable events or unintentional injuries or signs (including abnormal changes in laboratory values) that occurs in a study participant. An AE does not necessarily have to be causally related to the study. When an AE occurs, the principal investigator or co-investigators must take immediate and appropriate action and follow up on all patients experiencing the AE until symptoms resolve or clinically significant laboratory abnormalities return to baseline. All AEs will be evaluated and documented on the case report form (CRF). The information that will be collected about AEs will include their date of onset, severity, associated treatment, predictability, outcome, and causation. Additionally, a serious AE is defined as any untoward medical event that occurs at any dose, results in death, a life-threatening condition, requires hospitalization, and results in significant disability or incapacity. All serious AEs will be reported to the principal investigator and sent an e-mail to the manufacturers and distributors of imeglimin (Sumitomo Pharma Co., Ltd.) from the day they learn about serious adverse events to the next day. The principal investigator must report all AEs suspected of having causal relationships with the study to the CRB of Toho University.

### 2.5 Compensation for health hazards

There is no anticipated harm resulting from participation in this study, and participants will not receive compensation for their involvement. It is treated the same as the health hazard and medical accident which occurred in the usual medical care. The drugs prescribed in this study are appropriately used in accordance with the instructions of the doctor in charge, and if serious adverse events occur, they are subject to the application for relief benefits under the drug side effect relief system as in the case of daily medical care. The treatment for other side effects is carried out by insurance medical care. In addition, our clinic shall subscribe to the liability insurance for clinical research as a measure in the event of legal negligence in the case of health damage caused by this study.

### 2.6 Sample size calculation

The target sample size was set to 30.

No data on the effect of imeglimin on erythrocyte lifespan are available; however, in-house data from a Japanese phase 3 study conducted in 27 patients at our clinic showed that imeglimin significantly reduced hemoglobin levels in pre- and post-administration comparisons. Therefore, the sample size was determined based on these data. The mean hemoglobin levels before and 1 year after imeglimin administration were 15.2 and 14.5 g/dL, respectively, with a change of −0.7 g/dL. The standard deviation of the change was 0.8 g/dL; however, in this study, we estimated 1.0 g/dL to account for the study variability. Therefore, the required sample size is 24 when the significance level *α* = 0.05 (two-sided) and the power (1-β) is 90%. Considering dropouts, the target sample size was set to 30. To ensure that enough participants enroll to achieve the target sample size, we have screened potential participants based on inclusion and exclusion criteria, and patients are referred to the study if applicable.

### 2.7 Data collection and management

The principal investigator and sub-investigators will fill in all of each patient’s data in a CRF. It is necessary that all data recorded in the CRF are consistent with the original material, unless data recorded directly in the CRF are used as the source material. During the study, the investigators will collect data at each visit in accord with the schedule in Table 1. All data recorded in the CRF will be checked by the data manager and will then be fixed/set. All study findings and documents will be made confidential, and patients will always be identified by their patient number, never by name. Confidential patient-identifying documents will be maintained by the investigators to preserve participant anonymity. Thus, data management, including coding, security, storage and cleaning, will be performed by investigators throughout the study. These study data (i.e., consent forms, questionnaires, data extracted from practice records) will be stored in a locked cabinet in the investigator’s office and will be archived at Naka Kinen Clinic for 5 years after study completion.

### 2.8 Statistical analysis

Summary statistics of the background data of the study participants will be calculated. For nominal variables, the numbers in each category and their percentages will be shown; for continuous variables, the numbers, mean, standard deviation, minimum, median, and maximum values will be calculated.

Two analysis groups will be used to assess the efficacy of this study: the full analysis set (FAS) and the per-protocol set (PPS), with FAS being the primary analysis. The FAS will be the population of eligible patients who received at least one dose of the study drug and have hemoglobin concentration measurements at baseline and at least one time point during the observation period. The PPS will be the population from the FAS, excluding those who deviated from the study protocol (e.g., use of prohibited concomitant drugs or study drug adherence of <80%). The safety analysis set (SAS) will be used to determine the safety of the study, and the SAS will be the population of patients who received at least one dose of the study drug and have data on any of the safety outcomes.

Summary statistics of hemoglobin levels before and at 6 months after imeglimin, the primary efficacy endpoint, will be calculated. A one-sample *t*-test or Wilcoxon’s signed rank test will be used to evaluate its statistical significance. For the secondary outcomes obtained from the metric data, summary statistics will be calculated for each observation point, a one-sample *t*-test or Wilcoxon’s signed rank test will be performed to evaluate statistical significance, and, if necessary, analysis of covariance, and multivariate analysis will be performed. If the data are non-normally distributed, appropriate data transformations will be applied. When statistical tests are conducted, the significance level will be set at 0.05 (two-sided), with the confidence coefficient for statistical estimation being 95% (two-sided).

In addition, the principal investigator and a biostatistician will confirm the detailed statistical analysis plan before the database is locked. All laboratory data are analyzed by an independent a biostatistician at the implemented in compliance with an outsourcing agreement.

### 2.9 Premature termination of the study

Given the short duration of the study and the minimal risks associated with participation, no interim analysis will be performed in this study. The decision to discontinue the study will be made by the principal investigator based on the following reasons: when a serious violation or non-compliance of the Clinical Research Act or research plan is found; in the case of obtaining a fact that undermines or may undermine ethical or scientific rationality; in the case of a request for discontinuation or recommendation by the administrator of the implementing medical institution, the Ministry of Health, Labour and Welfare, and the CRB; In the case where the principal investigator responsible for the research determines the discontinuation.

### 2.10 Confidentiality

Data containing personal information of the study subjects to be collected in this study will be deleted when transcribing from the electronic medical record to the CRF, and a study subject identification code will be assigned for the study. The study subject identification code is a number that has no regularity with the medical record ID, and the last two digits are assigned in the order of enrollment in the study. In addition, the principal investigator will prepare a list of study subject identification codes to identify individual study subjects and keep it locked in a lockable locker.

### 2.11 Access to data

The investigators must not disclose the information contained in the CRFs to third parties without written approval from the principal investigator, except for regulatory agencies. Only investigators can access data. The datasets used or analyzed will be available from the principal investigator on reasonable request after the study has been completed.

### 2.12 Audit of the study

In order to ensure the reliability of the study results, an audit will be conducted on whether the study was conducted in accordance with Japan’s Clinical Trials Act and research plans. The audit of this study will be independently implemented in compliance with an outsourcing agreement. An independent audit team will inspect Naka Kinen Clinic, the research institute to ensure study data quality.

## 3 Discussion

In this study, the effect of imeglimin administration on lowering blood glucose in type 2 diabetic patients with inadequate glycemic control will be measured using HbA1c, GA and 1,5-AG as indices. The divergence between HbA1c and the rate of blood glucose-lowering with GA and 1,5-AG will be evaluated whether HbA1c is an appropriate index for imeglimin administration. The effect of imeglimin on erythrocytes will also be examined as a cause of the divergence. If imeglimin lengthens erythrocyte lifespan, HbA1c is not an appropriate measure of the hypoglycemic effect of imeglimin in the early stages of administration, but GA and 1,5-AG are appropriate measures to evaluate instead. If imeglimin improves erythrocyte deformability, imeglimin may be a new treatment strategy for peripheral arterial occlusive disease, a chronic complication of T2D.

In the TIMES 1–3 studies, imeglimin, both as monotherapy and in combination with other antidiabetic drugs, slowly decreases HbA1c, reaching a plateau around 24 weeks after administration (Dubourg et al., 2021; Dubourg et al., 2022; Reilhac et al., 2022). Furthermore, the fasting blood glucose trend in the TIMES 1 (monotherapy) study (106 subjects) showed a large decline at week 4 and plateaued from weeks 8 to 24 (Pharmaceuticals and Medical Devices Agency, 2021). This observation differed from the slowly declining trend of HbA1c, which was measured simultaneously. We also reported in a retrospective observational study that, under routine medical care, imeglimin treatment of type 2 diabetic patients resulted in a slower decrease in HbA1c than GA, with a divergence in the rate of change between the two (Osonoi et al., 2022a; Osonoi et al., 2022b). These results suggest that HbA1c may appear to be high. To assess whether HbA1c is an appropriate measure, this study will ensure reliability by comparing HbA1c with the rate of decrease in blood glucose over time for GA or 1.5-AG and by measuring sustained blood glucose variability with FGM and its association with changes in these measures.

In general, HbA1c levels depend not only on blood glucose but also on erythrocyte lifespan. Therefore, shortening or lengthening erythrocyte lifespan results in falsely low or high HbA1c levels, respectively (Panzer et al., 1982; Waters et al., 1988). If HbA1c is falsely elevated by imeglimin, lengthening of erythrocyte lifespan is suggested, but erythrocyte lifespan has not been studied in routine practice. Thus, this study will examine hemoglobin concentration, erythrocyte lifespan, and erythrocyte deformability to determine the effects on erythrocytes. Furthermore, if imeglimin improves erythrocyte deformability, it is expected to have the potential to be effective in treating peripheral arterial occlusive disease, so an index of arteriosclerosis will also be measured.

Erythrocytes can deform and pass through capillaries flexibly (erythrocyte deformability), which improves blood flow through good blood circulation and oxygen transportation (Shigihara et al., 1993). Erythrocyte deformability is mainly dictated by three factors: geometric cell factors (surface area to volume ratio, morphological changes), internal cell viscosity, and cell membrane viscoelasticity (Mohandas et al., 1993). MCV is related to the surface area to volume ratio, and increased MCV improves erythrocyte deformability (von Tempelhoff et al., 2016). In addition, internal erythrocyte viscosity is dependent on hemoglobin concentration; viscosity increases non-linearly with increasing MCHC. and erythrocyte deformability decreases markedly (von Tempelhoff et al., 2016). In our retrospective observational study, imeglimin increased MCV and decreased MCHC (Osonoi et al., 2022b). These results suggest that imeglimin may improve erythrocyte deformability. Various blood rheology abnormalities have been reported in diabetes mellitus, and there are reports of decreased erythrocyte deformability (Shin et al., 2007). Therefore, the ability of imeglimin to improve erythrocyte deformability would greatly benefit patients with T2D.

Imeglimin is a drug with a novel mechanism of mitochondrial function improvement. It has been suggested that imeglimin converts nicotinamide (NAM) to NAM mononucleotide (NMN) via increased gene expression of NAM phosphoribosyltransferase (NAMPT) in the salvage pathway utilizing NAM in islet beta cells. Then, NAM adenine dinucleotide (NAD^+^) is synthesized from NMN by NMN adenylyltransferase (NMNAT), which may enhance insulin secretion as well as mitochondrial function (Hallakou-Bozec et al., 2021a). However, NMNAT is also expressed in the cytoplasm of human erythrocytes (Stefano et al., 2010). Mice lacking the NMNAT gene show a marked decrease in erythrocyte NAD^+^ levels and a shorter erythrocyte lifespan of about 10 days compared to that of normal mice (about 60 days), with most of them having deformed and abnormal morphology (Hikosaka et al., 2014; Yaku et al., 2019). Therefore, if imeglimin can increase erythrocyte NAD^+^ levels, it would affect erythrocyte lifespan and deformability (Figure 1).

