## Abstract

**Background:** Imeglimin is a novel type 2 diabetes (T2D) drug that is expected to improve mitochondrial function. In its phase 3 clinical trials in Japanese patients with T2D, the hemoglobin A1c (HbA1c) decrease following imeglimin administration was slow, reaching a plateau after 20–24 weeks of treatment. In general, the erythrocyte lifespan may be a factor when HbA1c shows an abnormal value. Therefore, this study will comparatively evaluate HbA1c and other markers of glycemic control in patients with T2D after imeglimin administration and also examine the effects of imeglimin on erythrocytes.

**Methods:** This single-arm, open-label, prospective, exploratory study is designed to evaluate the divergence between HbA1c and glycoalbumin (GA) or 1,5-anhydroglucitol (1,5-AG) and the glycemic reduction rate in 30 patients with T2D with inadequate glycemic control when imeglimin 2,000 mg is administered for 6 months. In addition, we will examine the effect on erythrocytes, the presumed cause of this divergence. We will measure sustained glycemic variability using flash glucose monitoring and examine the relationship between changes in these indices and HbA1c. Moreover, because prolonged erythrocyte lifespan is a possible cause of falsely high HbA1c levels, erythrocyte lifespan, erythrocyte deformability, and hemoglobin concentration will be evaluated as effects of imeglimin on erythrocytes. Furthermore, if imeglimin has an ameliorative effect on erythrocyte deformability, it may improve peripheral arterial disease; thus, we will also evaluate the toe-brachial pressure index, a measure of this effect.

**Discussion:** In this study, if imeglimin administration results in diverging rates of hypoglycemic effect between HbA1c and GA or 1,5-AG and prolongs erythrocyte lifespan, GA and 1,5-AG, rather than HbA1c, will be considered appropriate measures of the hypoglycemic effect in the early stages of imeglimin administration. If imeglimin improves erythrocyte deformability, it may also be a new treatment strategy for peripheral arterial disease, a chronic complication of T2D.

**Ethics and dissemination:** The study protocol was scientifically and ethically reviewed and approved by the Certified Clinical Research Review Board of Toho University (approval number: THU22002). The study protocol was registered in the Japan Registry of Clinical Trials (jRCT) in December 2022 (jRCTs031220489).

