Prolonging the erythrocyte lifespan with imeglimin administration would result in a relatively high HbA1c and a slower rate of glycemic reduction than with GA or 1,5-anhydroglucitol (1,5-AG), suggesting that evaluating the glucose-lowering effect of imeglimin using HbA1c underestimates its effectiveness. There have been no reports, other than ours, on the divergence between HbA1c and GA or 1,5-AG on the glucose-lowering effect of imeglimin in patients with T2D under clinical conditions, or on its effect on erythrocytes (Osonoi et al., 2022a; Osonoi et al., 2022b).

The purpose of the study described in this protocol is to confirm the divergence between HbA1c and the rate of glycemic reduction between GA and 1,5-AG in patients with T2D after treatment with 1,000 mg of imeglimin twice daily for 6 months. In addition, we aim to prospectively examine the effects on erythrocytes, the presumed cause of this divergence.

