#### 2.3.2 Secondary outcomes

Items 1–4 below will be compared between baseline (month 0) and each time point in the pre-observation, observation, and follow-up periods, and between 6 months after imeglimin administration and each time point in the follow-up period. The change from baseline (maximum and mean values) in the pre-observation and observation periods will also be evaluated.1. Erythrocyte lifespan

Erythrocyte lifespan is calculated by measuring the carbon monoxide (CO) concentration in exhaled breath using a Carbolizer (Taiyo Co., Ltd., Osaka, Japan) and using the Strocchi et al., formula shown below (Strocchi et al., 1992):

Erythrocyte lifespan (days) = K × hemoglobin (g/mL)/endogenous CO (ppm).

K = 1380 (conversion factor).2. Erythrocyte deformability

Erythrocyte deformability is measured using a blood fluidity measuring device MC-FAN (Optima Inc., Tokyo, Japan). The microchannel array passage time of 100 μL heparinized whole blood is an index for blood fluidity.3. Red blood cell count, white blood cell count, hemoglobin concentration, and hematocrit (Ht)4. Corpuscular constant (mean corpuscular volume: MCV, mean corpuscular hemoglobin concentration: MCHC, mean corpuscular hemoglobin content: MCH)

Items 5 and 6 below will be compared between baseline and the pre-observation or observation periods.5. Measured values of HbA1c, GA, and 1,5-AG, change from baseline, and percent reduction in blood glucose with baseline as 100% (percent reduction in blood glucose will also be compared between each index at each time point)6. GA/HbA1c and 1,5-AG/HbA1c ratios

For items 7 and 8 below, data measured by the FGM system using FreeStyle Libre Pro (Abbott Diabetes Care Inc., Alameda, CA, United States of America) will be used to compare baseline with each time point during the observation period (up to 3 months after imeglimin administration). FreeStyle Libre Pro should be used following the package insert.7. Change in mean daily glucose levels and percentage decrease in blood glucose (baseline is the day before imeglimin administration)8. Mean 14-day glucose levels, estimated HbA1c levels, glucose management indicator (GMI), and respective percentage decreases in glycemia (baseline is 14 days before imeglimin administration):

Estimated HbA1c (%) = (mean glucose [mmol/L] + 2.59)/1.59.

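### The Discussion sets HbA1c aside on longer erythrocyte lifespan alone, the Abstract also requires divergence, and no listed outcome or named analysis links the two

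*Protocol article*

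**What the plan says.** Two places state when HbA1c would be judged unsuitable early in treatment.

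- Section 3 (Discussion): "If imeglimin lengthens erythrocyte lifespan, HbA1c is not an appropriate measure of the hypoglycemic effect of imeglimin in the early stages of administration". Lifespan is the only condition in the sentence, which goes on to name GA and 1,5-AG as the suitable measures.
- Abstract (Discussion paragraph): GA and 1,5-AG are preferred to HbA1c "if imeglimin administration results in diverging rates of hypoglycemic effect between HbA1c and GA or 1,5-AG and prolongs erythrocyte lifespan". Here there are two conditions, joined by *and*.

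The causal aim appears in the Introduction, "we aim to prospectively examine the effects on erythrocytes, the presumed cause of this divergence", and again in section 3, "The effect of imeglimin on erythrocytes will also be examined as a cause of the divergence".

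Section 2.3.2 lists the comparisons. For lifespan and the other red-cell items: "Items 1–4 below will be compared between baseline (month 0) and each time point in the pre-observation, observation, and follow-up periods", and also between month 6 and follow-up. For HbA1c, GA, 1,5-AG and their ratios: "Items 5 and 6 below will be compared between baseline and the pre-observation or observation periods", with the addition in item 5 that "percent reduction in blood glucose will also be compared between each index at each time point". Item 9 compares measured with estimated HbA1c. The one association described in words concerns glucose monitoring and the glycemic indices: "by measuring sustained blood glucose variability with FGM and its association with changes in these measures". Section 2.8 plans one-sample tests for the secondary outcomes and allows covariance or multivariate analysis if needed, naming no variables.

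**The concern.** The two conclusions differ in one case that matters: lifespan rises but the indices do not diverge. The Discussion sentence then rejects HbA1c; the Abstract draws no conclusion.

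The second gap is between aim and analysis. The question is whether a longer lifespan explains why HbA1c falls more slowly than GA or 1,5-AG. The listed comparisons can show that lifespan changed and that the indices diverged. They do not ask whether the two go together across patients, or whether the lifespan change is large enough to produce the gap. The Introduction itself names other sources of divergence: a transient lag whenever glucose improves quickly, seen at 2 months with DPP-4 inhibitors, and altered erythrocyte production. It argues from retrospective data that the lag is not enough to explain imeglimin's divergence. Without a control arm, two changes seen together leave these explanations unseparated. A claim about which marker clinicians should trust could then rest on coincidence in time.

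**Working it through.** **1. The two conclusions side by side**

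| Result | Abstract | Discussion sentence |
|---|---|---|
| Longer lifespan and divergence | GA and 1,5-AG preferred | HbA1c not appropriate |
| Longer lifespan, no divergence | no conclusion | HbA1c not appropriate |
| Divergence, lifespan unchanged | no conclusion | no conclusion |

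They disagree in the second row.

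**2. Search for a link in sections 2.3.2 to 2.3.4 and 2.8**

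- Item 1 (lifespan): against baseline and against month 6.
- Item 5: each index against baseline, and the indices against each other.
- Item 6: GA/HbA1c and 1,5-AG/HbA1c ratios against baseline.
- Items 7 to 9: glucose monitoring and estimated HbA1c.
- Safety and exploratory outcomes: none pairs lifespan with a glycemic index.
- Section 2.8: no model relating them is named.

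Items 5, 6 and 9 therefore measure the divergence, and item 1 measures lifespan, but nothing joins them. Items 5 and 6 also stop at the observation period while item 1 runs into follow-up, so the listed comparisons would not show whether the two reverse together.

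**3. The plan's own figure (section 2.6)**

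Inputs: hemoglobin change 0.7 g/dL, SD 1.0, two-sided 0.05, power 90%.

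- Normal approximation: (1.960 + 1.282)² / 0.7² = 21.4, so 22.
- Paired *t*-test (noncentral *t*): n = 24, power 90.7%. This matches the stated 24.
- 24 / 0.80 = 30, so the target implies 20% dropout.

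The figure reproduces, but it is sized on hemoglobin, not on lifespan, divergence or their link.

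**4. What two separate tests can show**

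Assumption, not in the protocol: a true lifespan shift of 0.7 SD. The power of its one-sample test is then 0.907 (n = 24) or 0.959 (n = 30).

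- No true divergence, n = 24: the Discussion sentence, read as a significant increase, rejects HbA1c in about 91% of trials. Requiring a significant divergence as well gives 0.907 × 0.05 = 0.045 (simulated 0.044, counting divergence in either direction).
- Both shift by 0.7 SD but are unrelated across patients: both are significant in 0.907² = 0.82 (simulated 0.83) at n = 24, and 0.959² = 0.92 at n = 30.

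The two-condition form removes the first problem. It does not establish cause.

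**5. Why size matters**

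Assumption: HbA1c is proportional to lifespan. Shift = HbA1c × proportional lengthening, at an illustrative HbA1c of 7.0 to 7.5% (eligibility is above 6.5% and up to 8.5%).

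| Lengthening | HbA1c shift (points) |
|---|---|
| 3% | 0.21 to 0.23 |
| 5% | 0.35 to 0.38 |
| 10% | 0.70 to 0.75 |

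Section 2.3.2 calculates lifespan as a constant times hemoglobin over endogenous CO. The planning fall in hemoglobin, 0.7 / 15.2 = 4.6%, would by itself move calculated lifespan by −4.6% at constant CO. Changes of a few percent therefore need quantitative reading.

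**6. What a linking analysis could detect**

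Fisher *z*, two-sided 0.05, 80% power: r = tanh(2.80 / √(n − 3)).

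- n = 24: tanh(2.80 / √21) = 0.55
- n = 30: tanh(2.80 / √27) = 0.49

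These are simple correlations of change scores between patients. Adjusting for one covariate (n − 4 in place of n − 3) gives 0.56 and 0.50. An observed r of 0.3 would have a 95% CI of −0.12 to 0.63 (n = 24) or −0.07 to 0.60 (n = 30).

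**The case against.** Both conclusions are discussion prose in a study labelled exploratory, with its small single-arm design stated as a limitation. The sentences just before the quoted one say that the divergence will be evaluated and that erythrocytes are examined as its cause, so the sentence may take divergence for granted. This stands as a reason to treat the mismatch as probably loose wording. It does not remove it, because the conclusion as written has one condition.

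The strongest objection is that the linking model belongs in the statistical analysis plan. Section 2.8 permits multivariate analysis and says a detailed plan will be confirmed before database lock. A reader might infer that the causal question is never tested; the document does not support that. It supports only that no listed outcome or named analysis tests it. Nor is every quantity compared only with its own baseline, since items 5, 6 and 9 compare markers with each other.

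A reader might also infer that any lengthening, however small, disqualifies HbA1c, or that lifespan would be credited with the whole gap. The sentence sets no threshold but does not say the first, and neither place says the second.

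If HbA1c does scale with lifespan, as the Discussion presumes, true lengthening always raises HbA1c, and lengthening with exactly zero divergence cannot occur. That limits the 91% illustration. But the premise is what the study sets out to examine, and a small bias may not matter in practice.

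Finally, a regression slope is a poor gate. If lifespan lengthens similarly in everyone, the slope could be near zero although lifespan is the cause, and a positive slope in one arm would not prove cause. Both points stand and shape the fix.

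**Conclusion.** The point holds in limited form, as an inexpensive improvement and not a design failure. The Discussion and the Abstract reach the same conclusion from different conditions and must be reconciled. The stated causal aim has no listed outcome or named analysis behind it, although the divergence itself is well covered. The inconsistency and the missing link rest on the text alone. The 91%, 4% and 83% figures rest on an assumed 0.7 SD shift, and the HbA1c shifts on assumed proportionality and an assumed amount of lengthening. They illustrate the reasoning and predict nothing about this trial. The unseen analysis plan may already name a linking model; if so, only the wording change remains.

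**What to change.** 1. Reword the Discussion to match the Abstract, so that both divergence and lengthened lifespan are required, and describe the causal conclusion as exploratory.
2. Name one exploratory analysis. Across patients, regress the month 0 to month 6 change in HbA1c on the change in lifespan, adjusting for the change in GA; alternatively, use the change in the GA/HbA1c ratio as the response. Report the slope with a 95% CI.
3. Beside it, report the HbA1c shift predicted from the observed mean lifespan change, with the proportionality assumption stated, next to the observed gap in the same units.
4. Do not make the causal reading depend on the sign of the slope. If measured minus glucose-monitoring-estimated HbA1c at month 3 is also shown, note that it contains ordinary lag: the Introduction says HbA1c reflects 6 to 12 weeks, while the estimate uses 14 days of glucose.

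Cost: one reworded conclusion and one added analysis, with no new visits or measurements, since lifespan and blood tests are already scheduled monthly. The downside is precision. With 24 to 30 patients the estimate will be wide, and the causal statement may have to be weaker than the authors would like.
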